| DOSE-Non-adherence score 1 or higher consenting patients who have completed baseline assessment will be randomly assigned into the intervention group (app) or the control group (standard care). The CRC will use the Study ID list to perform randomization and randomly allocate patients via block randomisation method with random permuted block sizes of 4 and 6. The randomisation will be computed using the R statistical software package by a statistician who will not be involved in the recruitment process. The random block sizes will be used to allocate patients to the intervention and control groups at a 1:1 ratio. Study allocation based on assigned Study ID will only be made known to the patients from the attending CRC after eligibility and consent are sought. |
| Contraception and Pregnancy Testing |
| The use of contraception will not be considered in this study. Pregnant and breastfeeding women will be excluded from this study. |
| Study Visits and Procedures |

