| **Pre-screening, recruitment and Visit 1 (month 0)**  Primary care team will screen for non-adherence to statin using DOSE questionnaire, and if positive and primary care team will verbally explain the study to eligible patients. Should the patient be keen to participate in the study, the primary care provider will refer the patient to the CRC.  Upon recruitment and after randomisation, patients will be informed if they are allocated to be in the intervention or control group. Polyclinic CRCs will email a centralized team who are not involved in the screening and assessment of patients for the randomization outcome. Only the centralized team will have access to the randomization list that was pre-generated. The polyclinic CRCs will be blinded until the randomization outcome upon being informed.  CRC will administer the remaining questionnaires and take anthropometric measurements. Lastly, CRC will collect demographic and clinical information from electronic medical record.  **INTERVENTION:** Patients will be required to install the intervention app. The CRC will take the patient through the app features and answer any questions they may have.  Patients will receive curated, reliable and up-to-date medical information in an easily digestible and understandable format via in-app text message. The app can also send reminders via in-app text messages or push notifications to remind patients to take their medicine and their appointment dates. Our Artificial intelligence (AI)–based chatbots will prompt patients to engage in conversation to uncover their barriers to medication adherence and assist with setting personal goals.  **Follow-up Visits (Visit 2 @Month 3, Visit 3 @ Month 6 and Visit 4 @ Month 12**  The CRC will remind patients to bring their lipid-lowering medication before the study visits.  During the visit, the CRC will carry out pill counts, administer questionnaires and collect clinical information from electronic medical record. Anthropometric measurements will be taken at Visit 3 (month 6) only.  Clinical pharmacist will review clinical blood test results, monitor for safety and titrate lipid-lowering medications as required.  **Intervention Group:** Health coach will use the information gathered by the AI-based chatbot, such as patient's readiness to change, perceived barriers and misbeliefs to guide the targeted behavioural intervention via in-app text message or phone consultations. The scope of coaching will be strictly related to the medication adherence and general well-being. The coach will not start, stop, or titrate any medication.  **Focus group discussion (sub-study):** 30-50 Intervention patients who give consent for this substudy will be contacted by study team. The discussion will be held either in-person or virtually and will take approximately 3-4 hours. |

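### Sections 6.1 and 6.3 disagree on whether baseline measurement is finished before allocation is disclosed, and their wording conflicts on who carries out the randomisation

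*Protocol*

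**What the plan says.** **Order of baseline and allocation.** Section 6.1 (Randomisation and Blinding) states that "consenting patients who have completed baseline assessment will be randomly assigned into the intervention group (app) or the control group (standard care"). Section 6.3 (Study Visits and Procedures) describes Visit 1 differently. After the DOSE screen and referral it says: "Upon recruitment and after randomisation, patients will be informed if they are allocated to be in the intervention or control group". It then describes the email to the central team and the unblinding of the CRC. The next paragraph reads "CRC will administer the remaining questionnaires and take anthropometric measurements", followed by "Lastly, CRC will collect demographic and clinical information from electronic medical record". App installation for the intervention arm comes after that.

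**Who randomises.** Section 6.1 says: "The CRC will use the Study ID list to perform randomization and randomly allocate patients via block randomisation method". It adds: "The randomisation will be computed using the R statistical software package by a statistician who will not be involved in the recruitment process". Section 6.3 says: "Only the centralized team will have access to the randomization list that was pre-generated", and that CRCs stay blinded until told the outcome. Section 3.2 (Recruitment Process) likewise gives custody of the lists to a central team outside recruitment and assessment.

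**The concern.** The trial is open-label (section 1.2, Rationale for Study Design). The third secondary objective covers health motivation and attitudes, self-care efficacy, self-care behaviours and quality of life, and Table 1 schedules the psychometric battery at months 0, 3, 6 and 12. A patient who has just learned that they will, or will not, get an app and a coach may answer such items differently from one who does not yet know. The CRC taking blood pressure, weight and waist circumference would also know the arm.

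Section 10.2 plans between-group tests of changes from baseline to end of trial. A baseline already touched by allocation enters those comparisons directly. If the only baseline value on file was taken after disclosure, no later analysis can recover the undisturbed one.

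The CRC confirms eligibility, takes consent and later administers the questionnaires and pill counts. This is the person from whom upcoming allocations most need to be hidden, so the protocol should not leave the CRC's part in randomisation open to two readings.

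**Working it through.** The protocol gives no figure on this point, so the check is a comparison of text, with a short algebraic note on the direction of any bias.

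1. **Explicit timing rule.** Section 6.1 makes completed baseline assessment a condition of randomisation.

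2. **Visit 1 narrative.** Section 6.3 runs: screen, referral, randomisation and disclosure, email to the central team, remaining questionnaires and anthropometry, record extraction, app installation. The words *remaining* and *lastly* mark it as a sequence of steps. It does not say outright that the questionnaires follow disclosure; that is read from the order of the text.

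3. **Does another section settle it?**
   - Section 3.2 puts consent before any study procedure and randomisation after consent, without saying whether baseline is finished in between.
   - Table 1 lists the onboarding questionnaire, DOSE, psychometric battery and anthropometry at month 0 for both arms. It has no row for randomisation and gives no order within the visit.
   - The list of assessments in section 6 says that the CRC administers the questionnaires, but not when relative to allocation.
   - The last sentence of section 6.1 on disclosure requires eligibility and consent only, and does not mention baseline.

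   So nothing elsewhere resolves the difference between steps 1 and 2.

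4. **Which measures are exposed?**
   - Section 6.3 does not name the remaining questionnaires. DOSE is used at screening, so the natural candidates are the onboarding questionnaire and the psychometric battery.
   - The onboarding questionnaire is scheduled at month 0 only and has no change score. The psychometric battery is repeated and does.
   - The DOSE screen is done by the primary care team before referral. However, Table 1 also lists DOSE at month 0 and section 6 has the CRC administer it. The protocol does not say whether the screening DOSE serves as the baseline DOSE.
   - LDL-C is a blood test result taken from the record. Pill counts start at month 3 and have no baseline.

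5. **Direction of bias.** Let disclosure shift the recorded baseline difference (intervention minus control) by s, and suppose the follow-up value is not shifted by the same mechanism. A change-score estimate then has expectation (true effect − s). An estimate adjusted for baseline with slope b has expectation (true effect − b·s), where b equals the within-arm correlation rho if the standard deviations at the two times are equal. The protocol gives neither s nor rho, so this fixes the form of the bias and not its size.

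6. **Who randomises.** Section 6.1 has the CRC performing randomisation and allocating patients from a Study ID list. Sections 3.2 and 6.3 have the central team holding the randomisation list, with section 6.3 adding that no one else has access and that the CRC learns the arm by email. Generation of the sequence by an independent statistician fits both accounts and is not part of the conflict. Read literally, the CRC cannot both allocate patients and be merely the recipient of an allocation.

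**The case against.** The strongest reply is that the order in section 6.3 is inferred. Its paragraph on allocation is not strictly chronological: it mentions telling patients their arm before it mentions the email that must come first. *Lastly* places record extraction after the questionnaires and anthropometry, but places none of them relative to randomisation. The only explicit timing rule for baseline is the one in section 6.1, and it is the sound one. This stands as a limit on the claim: the protocol does not say that baseline is taken with the arm known. It does not remove the problem, because a coordinator working down the Visit 1 text would do things in that order.

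A reader might infer that allocation concealment fails because the CRC works the list. The documents do not support that. A Study ID list need not carry allocations; section 6.1 is compatible with the CRC assigning the next ID and the central team returning the linked arm. Central custody (section 3.2), exclusive access and CRC blinding until informed (both section 6.3) all point that way. What stands is that the section 6.1 wording is inconsistent with them.

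A reader might also put in an assumed shift of 0.1 to 0.2 SD and note that it rivals the small effect size, below 0.2, in section 10.1. That comparison follows from the numbers chosen. Nothing in the protocol suggests a shift of that size or its sign, and the effect size in section 10.1 is not tied to any of these scales.

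Finally, the reach is limited. The primary objective is adherence, and the exposed measures are mainly secondary and self-reported. That is correct, and the conclusion is confined accordingly.

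**Conclusion.** The protocol contradicts itself on Visit 1. Section 6.1 requires baseline before randomisation; section 6.3, on its natural though not explicit reading, places the remaining questionnaires and anthropometry after disclosure. Where section 6.3 is followed, knowledge of the arm can bias change-from-baseline and baseline-adjusted results for the secondary psychometric and quality-of-life outcomes. In a multicentre trial, different polyclinics may follow different sections. The size of the bias cannot be derived from the documents. The DOSE screen and LDL-C are largely unaffected; the status of any separate DOSE taken by the CRC at month 0 is unclear.

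The CRC's role in randomisation is a second inconsistency, of wording only. It should be removed because it concerns concealment, but the protocol taken as a whole points to central allocation.

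The conclusion rests on reading the Visit 1 text as a sequence of steps, and on patients' self-reports being open to influence by knowledge of their arm.

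**What to change.** In section 6.3, rewrite Visit 1 as an ordered list:

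1. Eligibility confirmed and consent taken.
2. All baseline questionnaires (including any baseline DOSE) and anthropometry completed and recorded.
3. CRC emails the central team.
4. Central team returns the allocation, and it is disclosed to the patient.
5. App installed for intervention patients.

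State whether the screening DOSE is the baseline DOSE; if it is not, the baseline DOSE belongs in step 2.

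In section 6.1, replace the sentence that has the CRC perform the randomisation. Say that the CRC requests an allocation for the assigned Study ID and that the central team issues it from the pre-generated list. Extend the disclosure condition there to include completed baseline as well as eligibility and consent.

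The cost is wording only: the same procedures at the same visit, with no added burden and no change to the sample size. If patients have already been enrolled, record for each one whether baseline was taken before or after disclosure, since that cannot be reconstructed from the protocol.

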| Rationale and justification for the Study |
| Rationale for the Study Purpose |
| 1. The incidence of AMI in Singapore is expected to rise by 194.4% (482 to 1418 per 100,000 population) from 2025 to 2050. Individuals aged 40–64 years will observe the largest increase in AMI incidence (114.0%), followed by those aged 15–39 years (93.2%) and those aged ≥65 years old (28.3%) [8]. 2. Poor medication adherence portends poorer health outcomes. In Singapore, around 60% of adults not taking their medications as prescribed (as above) and this creates a considerable economic and clinical burden to individuals and health systems. 3. The use of digital technology in medication adherence has continued to grow as more healthcare providers and patients recognise its benefits in improving adherence and overall health outcome [9,10]. Digital interventions have effectively helped patients manage their medication by reminding patients to take their medications on time and providing them with more information about their medications and treatment plan [11]. In the busy world today, the provision of appropriately timed and that perceived to be important would be key to effectively convince intentionally non-adherent patients to take their medicines as prescribed. |
| Rationale for Doses Selected |
| Dosing of lipid-lowering medications adhere to local and international guidelines where relevant. |
| Rationale for Study Population |
| Hyperlipidemia remains as one of the three leading metabolic risk factors underlying AMI onset by 2050 [8]. In recent study 3 Asian ethnicities with AMI, the incidence of hyperlipidemia is projected to increase by 205% (341 to 1041 per 100,000 population) from 2025 to 2050. Locally, the high poor-adherence rates form an important basis for more to be done to address root causes. |
| Rationale for Study Design |
| This study is a multicentre, open-label, two-arm parallel randomized controlled trial. We intent to randomly assign patients with hyperlipidaemia into one of the two groups: human coach-supported Digital/AI Personal Health Assistant app (intervention group) and standard care (control group) with a 1:1 allocation ratio. |
|  |
| **HYPOTHESIS AND OBJECTIVES** |
| Hypothesis |

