| We hypothesize that the use of a human coach-supported digital/AI personal health assistant (app) will improve adherence to cholesterol-lowering medications (statins with or without ezetimibe) among patients with hyperlipidaemia and suboptimal LDL-C control, when compared to standard care. |
| - 1. **Primary Objectives** |
| To evaluate the effectiveness of the human coach-supported digital/AI personal health assistant (intervention) on adherence to lipid-lowering medication at 6 and 12 months compared with those receiving standard care. |
| - 1. **Secondary Objectives**  1. To evaluate the impact of human coach-supported digital/AI personal health assistant on blood LDL-cholesterol levels at 6 and 12 months compared with those receiving standard care. 2. To evaluate the impact of human coach-supported digital/AI personal health assistant on atherosclerotic cardiovascular disease (ASCVD) risk at 6 and 12 months. 3. To evaluate the impact of human coach-supported digital/AI personal health assistant on health motivation and attitudes, self-care efficacy, self-care behaviours, and quality of life at 6 and 12 months. 4. To evaluate the acceptability of a new model of care 5. To evaluate the safety of a new model of care 6. To evaluate the (cost) effectiveness of human coach-supported digital/AI personal health assistant (intervention) on adherence to lipid-lowering medication at 12 months compared with those receiving standard care. |
| - 1. **Potential Risks and benefits:** |
| Potential Risks |
| There is minimal risk of loss of privacy breach associated with the use of mobile app. For example, if there is a data breach, someone who is not authorised could get information collected in the app. This chance is small, but it is not zero. There will be measures in place to minimum the risks in this study. |
| Potential Benefits |
| Patients in the intervention group will get full access the app and personalized Health Coaching sessions with a trained personnel to optimize management of their health condition for 12 months. |
| 1. **STUDY POPULATION** |
| List the number of patients to be enrolled. |

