| 1. **Clinical data:** Clinical data will be collected on a patient’s demographic details, past medical history, medication use, blood test results and anthropometric measurements. 2. **Questionnaires**: Onboarding questionnaire, DOSE Non-Adherence Measure and Psychometric Battery Questionnaires will be administered by the CRC 3. **Pill count**: Patients are required to bring along their prescribed lipid-lowering medications during their follow-up visits (@3m, 6m, and 12m). CRC will carry out pill counts with the patients during the visits. 4. **Medical care follow-up**: Standard-of-Care clinical pharmacist will follow-up with patients, titrating lipid-lowering medication (such as statin, ezetimibe etc) as required, and review and take action clinical blood test results (Appendix B; e.g lipid level, blood creatinine kinase and liver function tests where relevant). 5. **Human-AI-health coaching (For intervention only):** Health coach will use the information gathered by the AI chatbot to guide the targeted behavioural intervention during phone consultation. The scope of coaching will be strictly related to the medication adherence and general well-being. The coach will not start, stop, or titrate any medication. Coach will escalate concerns to clinical pharmacists when deemed fit. 6. **Focus group discussion (sub-study):** This will be conducted with a nested sample of 30-50 intervention group patients. The aims are: (a) to collect insights from intervention patients on their experiences with the app and human health coaching, (b) insights into which intervention components work best for them and under what circumstances, (c) insights into concerns which might impact intervention effectiveness, (d) factors that draw their participation and sustained engagement, (e) factors that deter them from sustainable engagement, (f) factors that may lead other CVD patients to be more inclined to partake in such a intervention and (g) ideas and suggestions to make the intervention more appealing and effective. |
|  |
| Randomisation and Blinding |

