| It is important to store the data securely and used in a way its integrity is not compromised. Data obtained from the app will be stored on a local secured cloud platform and only accessible to authorised study team members (PI, co-Is, CRCs, pharmacists). Clinical data will be stored in a secure database, accessible only to the PI, co-Is, CRCs, pharmacists. The use of the data from the study will be controlled by the PI. |
| **SAMPLE SIZE AND STATISTICAL METHODS** |
| Determination of Sample Size |
| A total of 376 patients (188 per arm) are to be recruited. The computation takes into account a) 5 level of significance, b) desired statistical power of at least 90%, c) the potential application of a mixed-effect model in view of the multi-centre design, and to cater for the random effects of repeated measurements, d) a small effect size to be detected (i.e., <0.2), e) fewer than 10 predictors to be accommodated in model building and f) no more than 20% drop outs. A post-hoc power calculation should be facilitated after the data analysis is performed. |
| Statistical and Analytical Plans |

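### Both adherence measures are taken by the CRC role, which knows the arm, introduces the app and may see app data, and no safeguard on outcome assessment is stated

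*Protocol*

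**What the plan says.** Section 1.2 (Rationale for Study Design) describes a "multicentre, open-label, two-arm parallel randomized controlled trial". The primary objective in Section 2 is the effect of the coached app "on adherence to lipid-lowering medication at 6 and 12 months compared with those receiving standard care". The protocol describes two adherence measures, the DOSE Non-Adherence Measure and pill counts. Table 1 schedules both at months 3, 6 and 12, with DOSE also at baseline.

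The CRC has these tasks:

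- **Allocation.** Section 6.1 says that the allocation "will only be made known to the patients from the attending CRC". Section 6.3 adds: "The polyclinic CRCs will be blinded until the randomization outcome upon being informed".
- **Onboarding.** For intervention patients, Section 6.3 says: "The CRC will take the patient through the app features and answer any questions they may have".
- **Assessment.** Section 6 has the CRC administer the questionnaires, and on pill counts it says: "CRC will carry out pill counts with the patients during the visits". Section 6.3 repeats this for each follow-up visit: "During the visit, the CRC will carry out pill counts, administer questionnaires and collect clinical information from electronic medical record".
- **Data access.** Section 9.2 makes app data "only accessible to authorised study team members (PI, co-Is, CRCs, pharmacists". Section 5.1 gives the app to the intervention arm only.

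A central team that does not recruit or assess patients holds the randomisation list (Sections 3.2 and 6.3).

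**The concern.** Patients cannot be blinded to an app with coaching, so the protection still available lies in how adherence is measured. The protocol specifies none. The central team protects allocation concealment, which is a separate matter from outcome assessment. Despite its title, Section 6.1 (Randomisation and Blinding) says nothing about who may assess adherence.

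Bias could enter in two ways. An intervention patient may be reluctant to admit missed doses to the role that introduced the adherence app. A pill count also leaves room for judgement, such as how to treat tablets left at home or whether to query an odd count, and an assessor who knows the arm may use that room differently between arms. Both would act on the primary outcome, and no analysis can remove them afterwards. Who measures the outcome, in what order and with what data access is trial conduct fixed in the protocol, so it is not a detail awaiting a statistical analysis plan.

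**Working it through.** **Step 1: does the text put these tasks in one role?**

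| Element | Protocol section | Finding |
|---|---|---|
| Trial is open-label | 1.2 | Yes |
| Primary outcome is adherence | 2 | Yes, at 6 and 12 months; no instrument named |
| CRC learns the arm | 6.1, 6.3 | Yes, and tells the patient |
| CRC introduces the app | 6.3 | Yes, intervention arm |
| CRC may see app data | 9.2 | Yes, listed |
| CRC takes both adherence measures | 6, 6.3 | Yes |
| Same individual for one patient | none | Not stated, not excluded |
| Separate or blinded assessor, or adherence source outside the CRC | none | Not stated |

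**Step 2: how much bias would matter?** The protocol gives no figure for measurement bias, so there is none to reproduce. What follows is an illustration.

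Inputs from the protocol:
- 188 patients per arm and at most 20% drop-out (Section 10.1)
- two-sided 0.05 tests (Section 10.2)

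Evaluable patients per arm: 188 × 0.8 = 150.4, taken as 150.

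Assumed inputs:
- a true effect of zero
- a differential measurement shift b of 0.1, 0.2 or 0.3 SD
- a single two-mean z-test, which the protocol does not fix as its primary analysis

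The standard error of the difference in SD units is √(2/n), so the test statistic is centred at b × √(n/2). The chance of a significant result is P(|Z + b√(n/2)| > 1.96).

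For n = 150, √(150/2) = √75 = 8.660:
- b = 0.1: centre 0.866; P(Z > 1.094) = 0.137, plus about 0.002 from the other tail, gives 0.139.
- b = 0.2: centre 1.732; P(Z > 0.228) = 0.410.
- b = 0.3: centre 2.598; P(Z > −0.638) = 0.738.

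For n = 188 (no drop-out), √94 = 9.695, and the same steps give 0.163, 0.492 and 0.829.

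| Assumed shift | 150 per arm | 188 per arm |
|---|---|---|
| 0 | 5% | 5% |
| 0.1 SD | 14% | 16% |
| 0.2 SD | 41% | 49% |
| 0.3 SD | 74% | 83% |

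These percentages follow from the assumed shift for any two-arm trial of this size. They show how sensitive the result would be to bias, and are not evidence that bias of this size will occur.

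**The case against.** The strongest reply is that this is a common limitation of open-label trials, openly declared, and that several stronger readings go beyond the text. Much of that stands.

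- **One person.** A reader might infer that the individual who introduced the app also takes the patient's answers and counts the pills. The protocol describes a role, and speaks of polyclinic CRCs in the plural. It leaves the point open.
- **Inseparability.** A reader might infer that a positive adherence result could never be told apart from a measurement effect. That overlooks LDL-C, a secondary outcome at the same 6 and 12 months, which neither patient nor CRC can shade. It is an imperfect check, because pharmacists titrate lipid-lowering medication in both arms (Sections 6 and 6.3), but it is a check.
- **Direction.** Bias favouring the app is plausible but not established. Section 6.3 has the chatbot prompt patients to talk about their barriers, which could make intervention patients more candid about missed doses.
- **Comparison with the target effect.** Section 10.1 gives the effect size as below 0.2 with no metric, so a 0.2 SD shift cannot be equated with the effect sought.
- **Coaching at the visit.** Table 1 marks coaching in the follow-up columns, but Section 6.3 has a health coach deliver it by in-app message or telephone. The table does not show coaching inside the assessment visit.
- **Interviewing and app data.** Administration by the CRC need not mean reading DOSE aloud; Section 8.3 refers to completed questionnaires kept in a locked cabinet. Section 9.2 grants access to app data but does not say that CRCs consult them when assessing.

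None of this supplies a safeguard. The protocol does not require self-completion, separation of duties or restricted data access, and it describes no adherence measure outside the CRC role.

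**Conclusion.** The point holds as a weakness in how the primary outcome is measured. The role that knows the arm, introduces the app and may see one-arm data takes both described adherence measures, with no stated safeguard. Differential bias could therefore contribute to an adherence difference. The documents do not show that it will, nor how large it would be. Under the stated assumptions, a shift of 0.1 to 0.3 SD would raise the chance of a false significant result from 5% to between 14% and 74% with 150 per arm.

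The trial can run as designed, but the changes cost little and should be made. They will not remove the unblinded patient's own reporting bias, which the report should acknowledge.

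**What to change.** 1. **Sections 6 and 6.3:** have the patient self-complete DOSE at months 3, 6 and 12, before the pill count and pharmacist review, and return it sealed or directly to the database.
2. **Section 9.2:** remove CRC access to individual app data. General questions about app features can still be answered without it.
3. **Section 6.3:** where a polyclinic has more than one CRC, have the pill count done by a CRC who did not onboard that patient.
4. **Sections 6 and 10.2:** if prescription or dispensing entries are in the medical record already accessed (an assumption; the protocol mentions only medication use and medications), add a supportive record-based adherence measure for both arms, such as proportion of days covered. Use a fixed rule-based extract, or existing staff who hold neither the randomisation list nor app data. The central team is unsuitable because it holds the list.
5. **Section 10.2:** state that the adherence result will be interpreted alongside LDL-C, noting the limit that titration sets.

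The cost is protocol wording, a change of access rights and some programming for the record-based measure. Self-completion may leave slightly more DOSE items missing. No extra staff, visits or patients are needed.

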| **Table 1: Summary of Study Schedule**   \|  \| **Visit 1** \| **Visit 2** \| **Visit 3** \| **Visit 4** \| \| --- \| --- \| --- \| --- \| --- \| \|  \| **0m** \| **3m (± 2 weeks)** \| **6m (± 2 weeks)** \| **12m(± 2 weeks)** \| \| **Informed consent** \| **I, C** \|  \|  \|  \| \| **Collect demographic information from electronic medical record** \| **I, C** \|  \|  \|  \| \| **Download and install app** \| **I** \|  \|  \|  \| \| **Collect clinical data from electronic medical record** \| **I, C** \| **I, C** \| **I, C** \| **I, C** \| \| **Anthropometric measurements: Blood Pressure, height, weight, waist circumference** \| **I, C** \|  \| **I, C** \|  \| \| **Pill counts** \|  \| **I, C** \| **I, C** \| **I, C** \| \| **Questionnaires** \| \| \| \| \| \| - **Onboarding questionnaire** \| **I, C** \|  \|  \|  \| \| - **Dose Non-Adherence Measure** \| **I, C** \| **I, C** \| **I, C** \| **I, C** \| \| - **Psychometric Battery Questionnaires** \| **I, C** \| **I, C** \| **I, C** \| **I, C** \| \| **Clinical Pharmacist follow-up/review** \|  \| **I, C** \| **I, C** \| **I, C** \| \| **Human-AI-health coaching** \|  \| **I** \| **I** \| **I** \|   I = intervention, C = control |
| STUDY DESIGN |
| Summary of Study Design |
| This study is a multicentre, randomized controlled trial (RCT) on 376 hyperlipidaemia patients who are nonadherent to statins, with suboptimal LDL-C levels. These patients will be randomly assigned into one of the two groups: intervention group or standard care (control group) with a 1:1 allocation ratio. The intervention group will receive personalised feedback through the app coupled with human coaching on top of usual clinical care for cholesterol management. The control group will receive usual standard of care for lipid management but will not receive the personalised app nor have access to health coaching. |
| **METHODS AND ASSESSMENTS** |

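### ASCVD risk is an outcome at 6 and 12 months, but no study blood pressure is scheduled at month 12, so the 12-month score would rest on an unspecified routine reading.

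*Protocol*

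**What the plan says.** **Objective.** Item 2 of the Secondary Objectives (protocol section 2) is the effect of the intervention "on atherosclerotic cardiovascular disease (ASCVD) risk at 6 and 12 months".

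**Schedule.** Table 1 (section 4) has a row "Anthropometric measurements: Blood Pressure, height, weight, waist circumference". It is filled for intervention and control at Visit 1 (month 0) and Visit 3 (month 6). The cells for Visit 2 (month 3) and Visit 4 (month 12) are empty.

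**Visit procedures.** Section 6.3 says of Visit 1: "CRC will administer the remaining questionnaires and take anthropometric measurements". Of the follow-up visits it says: "Anthropometric measurements will be taken at Visit 3 (month 6) only".

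**Record data.** A separate row of Table 1, "Collect clinical data from electronic medical record", is filled for both arms at all four visits. Item 1 of section 6 says that clinical data cover demographics and "past medical history, medication use, blood test results and anthropometric measurements". For the follow-up visits, section 6.3 has the CRC "administer questionnaires and collect clinical information from electronic medical record", without listing the items.

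**The concern.** An outcome defined at a given time needs its components at that time. Blood pressure is a usual component of an ASCVD risk score, and the schedule leaves it out at the later of the objective's two time points. What is at stake is whether the 12-month score can be computed for most patients, and whether it means the same thing as the score at baseline and month 6. A missed reading cannot be recovered once Visit 4 has passed. A statistical analysis plan can name the score or say how to handle gaps, but it cannot supply a measurement that the visit schedule does not call for.

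**Working it through.** The plan states no figure to reproduce, and the point does not depend on alpha, power or effect size. The check sets the objective against the schedule.

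| Month | ASCVD risk required (section 2) | Study blood pressure (Table 1, section 6.3) | Record data collected (Table 1) |
| --- | --- | --- | --- |
| 0 | baseline for comparison | yes, both arms | yes, both arms |
| 3 | no | no | yes, both arms |
| 6 | yes | yes, both arms | yes, both arms |
| 12 | yes | **no** | yes, both arms |

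1. *Is the gap an artefact of a broken table?* No. Table 1 and the text of section 6.3 agree, and the text restricts follow-up anthropometry to month 6 in so many words. That sentence stands under the follow-up visits, so it does not conflict with the baseline measurement.

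2. *How much of the objective is covered?* Of its two time points, month 6 has a study blood pressure and month 12 has none: 1 of 2.

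3. *Can the record fill the gap?* Possibly. Data are drawn from it at month 12, and section 6 counts anthropometric measurements among clinical data. But nothing requires a blood pressure to be recorded near month 12, sets a window for one, or says which value enters the score. Table 1 also keeps the record data and the anthropometric measurements in separate rows. The examples of record content in the discontinuation procedures (an open list) are drugs, laboratory results and clinical events, with no mention of blood pressure.

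4. *What follows for the score?* At months 0 and 6 the reading is taken at the study visit. At month 12 it would be a routine one, at a time the study does not control, or absent. A change from baseline or from month 6 would then mix a true change with a change in how blood pressure was obtained. Patients without a reading would have no 12-month score.

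5. *How many patients?* At most 376 × 1 = 376. With drop-out at the 20% allowed for in section 10.1, 376 × (1 − 0.20) = 300.8, or about 301. How many would lack a usable routine reading cannot be worked out from the protocol.

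**The case against.** The strongest reply is that routine records are this protocol's normal source. Table 1 has no row for a study blood draw, and blood results are collected as clinical data and reviewed by the standard-of-care pharmacist, so the lipids appear to come from routine care as well. A record value at month 12 is then no failure in itself, and the choice of reading and window could be left to a statistical analysis plan. Much of this stands. A reader might infer that the 12-month objective cannot be answered at all; the documents do not support that, because the month-12 record data may well contain a blood pressure. What remains is that the protocol chose to measure blood pressure itself at months 0 and 6, and so changes the basis of the outcome at month 12 without saying so.

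A reader might also infer that routine readings would differ between arms, because the intervention arm has more contact. The documents do not show this. The extra contact is through the app or by phone, no coach is said to measure blood pressure, and study visits and pharmacist review are scheduled alike in both arms at months 3, 6 and 12.

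Nor does the protocol say that the month-6 value would be carried forward. Its imputation rule in section 10.2 concerns unanswered items within a score.

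Finally, the risk score and its inputs are not named. That objection is fair and limits the confidence of the finding.

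**Conclusion.** The mismatch between objective and schedule is real: ASCVD risk is wanted at month 12, and no study blood pressure is scheduled then. The 12-month score is not impossible to compute, but as planned it would rest on a reading that is neither required nor timed, would be missing where none exists, and would not be comparable in method with baseline and month 6. The cost is in completeness and consistency over time; no bias between arms has been shown.

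The conclusion assumes that the score uses systolic blood pressure, which is plausible but comes from outside the document. Confidence is therefore moderate. The effect is limited to one time point of one secondary objective. The adherence and LDL-cholesterol objectives are untouched. It is worth correcting because the correction is small and must be made before patients reach Visit 4.

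**What to change.** Preferred: in Table 1, mark the anthropometric row (at least blood pressure) for both arms at Visit 4, and change the section 6.3 sentence so that follow-up anthropometry is taken at Visit 3 (month 6) and Visit 4 (month 12). The cost is, by estimate, a few minutes per patient at a visit where the CRC already does pill counts and questionnaires.

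If the sponsor does not want the extra measurement, either of two changes of wording would reconcile the sections:

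- Name the electronic record as the source of the month-12 blood pressure, with a fixed window around Visit 4 and a rule for choosing among several readings. This costs nothing at the visit, but leaves the change of method and the missing readings in place.
- Limit the ASCVD risk objective to 6 months. This is the simplest edit, but it gives up the final time point of the objective.

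In each case, name the risk score and its inputs, so that the schedule can be checked against them.
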